#### Predictive analyses

We will implement both basic and advanced models and compare subsets of data and different timeframes to balance interpretability and predictive performance. With a sample size of at least 350 participants, we have sufficient data to explore a range of methods.

There are various ways to aggregate and preprocess EMA data to include them as predictors of non-response, ranging from simple aggregates to advanced modelling techniques. We will implement dynamic structural equation models (DSEM), an advanced extension of multilevel modelling that integrates time-series dynamics with latent variable modelling.^30^ Multilevel models are considered the gold standard for longitudinal data analysis in psychology,^31^ and DSEM builds on this foundation to allow unequally spaced observations and modelling of time-lagged dependencies, making it well suited for EMA data. The Bayesian estimation approach allows for missing data under the missing at random assumption (eg, when participants skip measurements). Beyond that, DSEM models are extendable to model change in dynamic parameters across measurement bursts. Further, passive data can be flexibly integrated into DSEM to analyse cross-lagged relationships between EMA (ie, affect) and passive sensing features (ie, sleep and physical activity). The model-based framework allows us to derive dynamic parameters (eg, individual autocorrelations and cross-lagged relationships) that we will use as features for the predictive analyses.

For the prediction of NR, basic algorithms include logistic regression, support vector machines, random forests and gradient boosting, depending on the research question and predictors used. Tree-based approaches are known for their effectiveness on tabular data.^32^ Regression-based approaches are highly interpretable. All of the selected require fewer computational resources compared with deep learning models and were frequently applied in psychotherapy research, increasing comparability.^33^,^35^

Advanced modelling approaches will be selected to incorporate the hierarchical, sequential and multimodal structure of our data. These include deep learning architectures like LSTM, Transformers or ensemble learning approaches. To explore how the predictive capacities depend on the time lag, we compare the accuracies of models using subsets of available data (eg, first measurement burst vs second measurement burst) and outcome timepoints (ie, T20 vs TPost).

As outlined above, we are interested in the incremental value of DP and EMA data to less burdensome, cross-sectional self-reports. As a first step, we will construct a baseline model that relies exclusively on the cross-sectional information collected at enrolment (T0).

Predictors will mirror the variables listed in the main protocol^1^—emographics, clinical routine variables (ie, primary diagnosis, comorbidity, medication and previous CBT) and standard intake questionnaires. Separate models will be trained for our two prespecified outcomes (T20, TPost). The baseline cross-sectional models will be compared against four progressively richer model sets: (a) EMA-only models, (b) passive-sensor-only models, (c) EMA+passive-sensor models and (d) all data sources combined (T0+EMA + passive). Paired differences in area under the curve (with 95% CIs, DeLong test) will quantify improvements in discrimination of (non)-response.

To assess feature importance and increase interpretability of our models, we will implement model-agnostic SHapley values (SHAP, SHapley Additive exPlanations).

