Our research objectives encompass predictive and exploratory hypotheses. First, in-line with PREACT, we aim to find out if we can predict non-response (NR) at T20 (ie, after 20 therapy sessions) and TPost (ie, after therapy end or 365 days if therapy lasts longer) with sufficient predictive accuracy (i.e. >75%) using a combination of EMA and passive sensing features collected during the first, 14-day assessment phase (T0). We expect that EMA-based features can better capture ER-related dynamics and are thus of greatest importance, but passive features will provide significant incremental value. We further hypothesise that EMA and sensing features both have an incremental predictive value beyond more elaborate (neuro)physiological markers and thus represent an ecologically valid substitute for implementation. Second, we aim to find out if symptom changes during CBT can be modelled using EMA and passive sensing, and how they relate to cross-sectional self-report and physiological information. We hypothesise that data actively and passively generated by personal electronic devices such as smartphones and wearables can be linked to neuroimaging-based markers of ER assessed in other subprojects of the research group.

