### Data preprocessing and feature engineering

In its raw format, passive sensing data are usually not interpretable. Thus, depending on the data source, data format and research question, different data preprocessing and aggregation steps will be necessary.

GPS data are collected as tuples containing coordinates (ie, Latitude and Longitude values). To clean and preprocess the data and build ML features, we follow guidelines by Müller *et al* (35). We adapt them to our event-based sampling format, where GPS was assessed when a location change was detected. From GPS data, we will calculate movement patterns in predefined timescales, that is, location entropy, distance travelled or time spent at home.Passive data derived from the Withings Scanwatch will be further preprocessed where possible and necessary, as Withings does not provide raw data for most data sources (see table 1). Here, we align our preprocessing steps with guidelines for preprocessing sensor data (36). From continuous PPG-based heart ate data, we are able to build features like average HR, min/max HR and HR-zones. From the resting-state ECG,we can create more fine-grained features like HRV. For sleep, we will calculate features describing sleep quality, that is, sleep duration, proportion of sleep phases and sleep efficiency (i.e. sleep duration/ time in bed) per night. Activity features describe the amount of, or time in active or inactive states, that is, total number of steps or time spent walking/running/cycling and the amount of calories burned.For EMA data, we will calculate the RMSSD (that is, for emotional inertia or ER variability), individual SD and mean values. Further feature engineering steps for EMA are described in the *Analysis* section.

Depending on the research question and granularity of data aggregation, a certain compliance rate has to be met to be included in the analysis (ie, at least 50% of completed EMA beeps). Missing data imputation will also depend on the type of data and applied analyses.

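### The listed model comparisons do not match the incremental-value hypotheses: three of four contrasts measure replacement, none isolates passive sensing over EMA, and none includes a neurophysiological model

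*Protocol article*

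**What the plan says.** The last paragraph of the Introduction sets out the hypotheses. EMA features are expected to matter most, and "passive features will provide significant incremental value". The authors also hypothesise that EMA and sensing have "incremental predictive value beyond more elaborate (neuro)physiological markers and thus represent an ecologically valid substitute for implementation".

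The Predictive analyses section opens its comparison plan by referring back to those aims, but words the interest as follows: "we are interested in the incremental value of DP and EMA data to less burdensome, cross-sectional self-reports". The reference model uses only cross-sectional enrolment (T0) data: demographics, routine clinical variables and intake questionnaires. Then: "The baseline cross-sectional models will be compared against four progressively richer model sets: (a) EMA-only models, (b) passive-sensor-only models", followed by (c) EMA plus passive and (d) all sources, spelled out as T0, EMA and passive. Separate models are trained for the T20 and TPost outcomes. Paired AUC differences with 95% confidence intervals and the DeLong test quantify improvement. SHAP values describe feature importance.

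EEG and MRI appear in the analysis plan only as stratification variables for the hold-out sample (Data freeze, holdout and model training).

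**The concern.** An increment is what a block of predictors adds to a model that already contains the comparator. That requires nested models. Here three of the four sets called richer drop the comparator, and the fourth adds two blocks at once. The hypotheses about passive sensing and about neurophysiological markers therefore have no named contrast.

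The practical risk is misreading. An EMA-only model that fails to beat the T0 baseline could be reported as EMA having no incremental value, although adding EMA to T0 would improve prediction. A gain for (d) could be credited to passive sensing when EMA produced all of it. And if the missing contrasts are chosen once results are known, they are no longer prespecified tests of the hypotheses.

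**Working it through.** **1. Nesting check.** Write each model as its set of predictor blocks, with the baseline B = {T0}.

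| Set | Blocks | Drops from B | Adds to B | Nested in B? |
|---|---|---|---|---|
| (a) | EMA | T0 | EMA | no |
| (b) | passive | T0 | passive | no |
| (c) | EMA, passive | T0 | EMA, passive | no |
| (d) | T0, EMA, passive | none | EMA, passive | yes |

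Here nested means that the set contains the whole baseline. With two outcome times there are 4 × 2 = 8 listed contrasts, and 1 × 2 = 2 of them measure an increment. Set (b) is not richer than (a) either.

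**2. Hypotheses against contrasts.**

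- *Passive adds value alongside EMA.* This needs EMA+passive against EMA, or T0+EMA+passive against T0+EMA. Listed: 0 of 4. If the sentence is read instead as passive over T0, it needs T0+passive against T0, which is also not listed.
- *EMA and sensing each add beyond neurophysiological markers.* This needs a model holding those markers, with and without each digital block. Listed: 0 of 4.
- *Digital data add to self-reports* (the wording in the analysis section). The joint form is tested by (d) against B. The separate forms, T0+EMA against T0 and T0+passive against T0, are not listed.

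**3. Can the wrong contrast mislead?** The article gives no block AUCs, so those below are assumptions. For independent binormal blocks, AUC = Φ(√Σz²), where z = Φ⁻¹(AUC of each block). With T0 0.70, EMA 0.65 and passive 0.60, z² is 0.275, 0.148 and 0.064.

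- (c): Φ(√0.213) = 0.678, so (c) − B = −0.022.
- (d): Φ(√0.488) = 0.758, so (d) − B = +0.058.
- T0+EMA: Φ(√0.423) = 0.742, so EMA given T0 = +0.042.

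The same calculation for four assumed sets of block AUCs (T0, EMA, passive):

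| Assumed AUCs | a−B | b−B | c−B | d−B | EMA given T0 | Passive given T0 | Passive given EMA | Passive given T0+EMA |
|---|---|---|---|---|---|---|---|---|
| 0.70, 0.65, 0.60 | −0.050 | −0.100 | −0.022 | +0.058 | +0.042 | +0.020 | +0.028 | +0.015 |
| 0.70, 0.70, 0.60 | 0.000 | −0.100 | +0.020 | +0.083 | +0.071 | +0.020 | +0.020 | +0.013 |
| 0.65, 0.70, 0.60 | +0.050 | −0.050 | +0.070 | +0.108 | +0.092 | +0.028 | +0.020 | +0.015 |
| 0.70, 0.60, 0.55 | −0.100 | −0.150 | −0.089 | +0.024 | +0.020 | +0.005 | +0.011 | +0.004 |

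Every true increment is positive, while (c) − B runs from −0.089 to +0.070 and (b) − B is always negative. If passive were pure noise in the first scenario, (d) − B would still be +0.042, all of it from EMA.

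**4. Increment is not substitution.** Take the 0.70 block in the first row as any established marker. EMA adds +0.042 to it, yet EMA alone is 0.050 worse. Adding to a marker therefore does not show that the marker can be replaced. That takes a head-to-head comparison.

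**The case against.** Much can be said for the plan.

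- **The interest worded in the analysis section is tested.** (d) against baseline is a sound test of the joint increment over self-reports. The aim of more than 75% accuracy is unaffected. This stands.
- **Passive over EMA needs no new model.** (a) and (c) are both planned for both outcomes, and the sentence on paired AUC differences is not expressly limited to baseline contrasts. A reader might infer that the study cannot answer this question; the article does not support that. What remains is that the contrast is not named.
- **Replacement comparisons are legitimate.** (a) to (c) against baseline show whether digital data could stand in for intake data. The fault lies in presenting them as richer sets under an incremental aim.
- **Neurophysiological models may be defined elsewhere.** The article points to a main PREACT protocol and to OSF and GitHub, and the shared hold-out is stratified by EEG and MRI. A reader might infer that no such comparator exists anywhere; the article shows only that none is listed here. It nevertheless states the hypothesis as its own, refers back to it, and then names a different comparator.
- **SHAP bears on importance.** It does so descriptively and does not test an increment.
- **Different patients per model.** Because "a certain compliance rate has to be met to be included in the analysis" and the rate depends on the research question, a reader might infer that the paired tests run on unequal samples. The article does not say so, and paired differences already imply a common set.

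**Conclusion.** The mismatch is established from the text alone. Three of four listed contrasts drop the T0 predictors, the fourth joins EMA and passive, and none isolates passive over EMA or includes a neurophysiological model. The comparator also shifts from elaborate neurophysiological markers in the Introduction to self-reports in Predictive analyses, and the inference from increment to substitute does not follow.

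The AUC figures show only that the listed contrasts can carry the wrong sign for an increment question. They rest on assumed block AUCs and on independence between blocks, and they do not estimate what this study will find.

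A reader might also infer a large multiplicity problem: eight independent 5% tests give 1 − 0.95⁸ = 34%. That counts false differences in either direction. False improvements alone would be 1 − 0.975⁸ = 18%, and the contrasts share a baseline, so independence fails. Neither figure is part of this point.

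**What to change.** 1. Add two model sets: T0+EMA and T0+passive.
2. Name the increment contrasts, each on the same participants: T0+EMA against T0; T0+passive against T0; T0+EMA+passive against T0+EMA; and (c) against (a). Keep (d) against baseline as the joint increment.
3. Keep (a) to (c) against baseline, label them as replacement comparisons, and drop the description of these sets as progressively richer.
4. For the neurophysiological hypothesis, do one of three things. Define, in participants with EEG or MRI, those markers with and without EMA and with and without passive, plus a head-to-head comparison for the substitute claim. Or cite where this is defined. Or withdraw the claim. Align the comparator named in the Introduction with the one in Predictive analyses.

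The first three steps cost two extra model sets per algorithm and outcome, plus wording. No new data are needed, and the hold-out is described as untouched, so the contrasts can be named before it is used. Step 4 costs more if the comparison is to be built here.

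The downside is low precision in the hold-out. The planned samples reproduce: 585 × 0.80 = 468, and 468 × 0.75 = 351 (stated as 350). A 20% hold-out is then about 94 or 70 patients. In simulation under the first AUC scenario with 50% non-response (both assumed), the standard error of (c) minus (a) was about 0.035 at 94 and 0.041 at 70, larger than the increment of 0.028. Report AUC differences with confidence intervals, and do not read a non-significant hold-out result as absence of an increment.

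### Three of the four model sets compared with the T0 baseline omit the T0 predictors, so they show stand-alone performance, and no listed contrast isolates the increment of EMA or of passive sensing over T0

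*Protocol article*

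**What the plan says.** All of this is in the protocol article, Predictive analyses, unless noted.

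- Aim: "we are interested in the incremental value of DP and EMA data to less burdensome, cross-sectional self-reports".
- Reference: a baseline model built only on cross-sectional information from enrolment (demographics, routine clinical variables, intake questionnaires), fitted separately for T20 and TPost.
- Comparators: "four progressively richer model sets: (a) EMA-only models, (b) passive-sensor-only models, (c) EMA+passive-sensor models and (d) all data sources combined". The text spells out (d) as T0 plus EMA plus passive data.
- Measure: "Paired differences in area under the curve (with 95% CIs, DeLong test) will quantify improvements in discrimination of (non)-response".

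The Introduction has two related hypotheses. One, following a statement that EMA features should matter most, is that "passive features will provide significant incremental value". The other is that "EMA and sensing features both have an incremental predictive value beyond more elaborate (neuro)physiological markers".

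**The concern.** An increment over T0 is the gain from a model that holds the T0 predictors plus the new source, compared with the T0 predictors alone. Sets (a), (b) and (c) drop the T0 predictors. They are alternatives to the baseline, not extensions of it, yet their AUC differences are among those that "will quantify improvements in discrimination of (non)-response".

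The sign of such a difference does not answer the increment question. A source that predicts less well than T0 on its own may still add to it, and a source that equals T0 may be almost wholly redundant with it. A reader who takes the four differences as a graded answer to the stated aim could conclude that EMA or sensing adds nothing when it does. The reverse error is also possible. Nor can the one true increment, (d) versus T0, be divided between the two sources from the listed comparisons.

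**Working it through.** **Step 1. Which increments do the listed models identify?** Write each model as its set of predictor blocks: baseline {T0}; (a) {EMA}; (b) {passive}; (c) {EMA, passive}; (d) {T0, EMA, passive}. The nested pairs are:

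| Smaller | Larger | Block added |
|---|---|---|
| baseline | (d) | EMA and passive jointly |
| (a) | (c) | passive |
| (b) | (c) | EMA |
| (c) | (d) | T0 |
| (a) | (d) | T0 and passive |
| (b) | (d) | T0 and EMA |

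No pair adds EMA alone, or passive alone, to a model that already contains T0. The baseline is nested in (d) only, and (a) is not nested in (b), so *progressively richer* does not describe the sequence. This step needs no numerical assumption.

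**Step 2. How far apart can the two kinds of difference be?** The article gives no AUCs or between-source correlations, so every value here is assumed. With binormal scores, each block has separation d = √2·Φ⁻¹(AUC), and a combined model has AUC = Φ(√(d′S⁻¹d / 2)), where S is the correlation matrix of the block scores.

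Take AUCs of 0.70 (T0), 0.66 (EMA) and 0.60 (passive), so d = 0.742, 0.583 and 0.358. Take correlations of 0.3 (T0-EMA), 0.2 (T0-passive) and 0.2 (EMA-passive).

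- T0+EMA: d′S⁻¹d = (0.550 + 0.340 - 2·0.3·0.742·0.583)/(1 - 0.09) = 0.693, so AUC = Φ(√0.3465) = 0.722.
- T0+passive: (0.550 + 0.128 - 2·0.2·0.742·0.358)/(1 - 0.04) = 0.596, so AUC = 0.707.
- Set (c): AUC 0.673. Set (d): AUC 0.726 (0.7255).

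Planned differences from T0: (a) -0.040, (b) -0.100, (c) -0.027, (d) +0.026. Increments over T0: EMA +0.022, passive +0.007. Three of the four planned differences are negative although both sources add.

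**Step 3. Can the planned differences separate the sources?** Take AUCs 0.70, 0.65 and 0.60 and an EMA-passive correlation of 0.2.

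| T0-EMA, T0-passive correlation | (a)-T0 | (b)-T0 | (c)-T0 | (d)-T0 | EMA over T0 | Passive over T0 |
|---|---|---|---|---|---|---|
| 0.2, 0.5 | -0.050 | -0.100 | -0.035 | +0.025 | +0.025 | 0.000 |
| 0.8, 0.0 | -0.050 | -0.100 | -0.035 | +0.026 | +0.001 | +0.020 |

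The planned differences are practically the same in both rows, while the source of the gain is reversed. Likewise, if EMA alone has the same AUC as T0 (0.70, difference 0.00), its increment is +0.005 at a T0-EMA correlation of 0.9 and +0.051 at 0.2.

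**Step 4. How precisely could the missing increments be estimated?** Sample size calculation gives 585 × 0.80 = 468 patients at T0 and 468 × 0.75 = 351 (stated as 350) in the long version. A 20% hold-out is 0.20 × 350 = 70 to 0.20 × 468 = 93.6, about 94. Assume AUC 0.70, non-response of 40% to 60%, and a correlation ρ of 0.5 to 0.9 between the paired AUC estimates. The Hanley-McNeil standard error of one AUC is about 0.054 to 0.066, and the 95% half-width of a paired difference is 1.96·SE·√(2(1 - ρ)), about 0.05 to 0.13. That is larger than the increments of about 0.01 to 0.03 in Step 2.

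**The case against.** **The aim can be read as joint.** The sentence does not say that each source is to be assessed separately, and the Introduction defines digital phenotyping as the combination of active and passive data. On that reading (d) versus T0 is the right nested contrast, and it is planned. This stands: a reader might infer that no increment over T0 can be estimated, and that would be wrong. It does not rescue (a) to (c), which are offered alongside (d) as measuring improvement.

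**The Introduction's hypotheses are not defeated.** In context, the passive-sensing hypothesis reads most naturally as passive over EMA. That is obtainable as (c) minus (a), although the text names only comparisons with the baseline. The hypothesis about both sources refers to (neuro)physiological markers, not T0 self-reports. This stands too.

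**Stand-alone models are legitimate.** They are, their labels are transparent, and they should be kept. The fault lies in the question they are said to answer.

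**Other parts of the plan may cover it.** SHAP values attribute a model's output to its features; they do not give an AUC gain over T0. The planned comparison of data subsets is illustrated by measurement bursts, not by T0+EMA or T0+passive. The analysis procedure on OSF and GitHub is not at hand and may hold more models, so the missing increments are best described as absent from the listed contrasts. The data would allow them.

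**The repair buys little precision.** Step 4 supports this. A reader might infer that two added models would show which source earned the gain, or that the study must choose between EMA and sensing. The documents state no such choice, and a hold-out of this size could not settle it. Nor can sensing simply be called the low-burden option: the Discussion counts continuous watch wear, including at night, as part of the burden.

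**Conclusion.** The point holds in limited form. Of the four comparisons with the T0 baseline, one measures an increment (the joint one) and three measure stand-alone or replacement performance. *Progressively richer* is a misdescription, and neither source's own increment over T0 is among the listed contrasts. These conclusions follow from the model definitions alone.

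The numerical size is illustrative. Under the assumed AUCs and correlations, stand-alone differences of about -0.03 to -0.10 coexist with real increments of about +0.01 to +0.03. The gains are modest, and their estimates on the hold-out would be wide. This is an inexpensive correction that lines the comparisons up with the stated aim; it does not invalidate the predictive analysis.

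**What to change.** In Predictive analyses:

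1. Name (d) versus T0 as the contrast for the joint increment of EMA and passive data.
2. Add T0+EMA versus T0 and T0+passive versus T0, on the same patients, reported as paired AUC differences with 95% CIs.
3. Keep (a), (b) and (c) versus T0, label them stand-alone performance (possible replacement of T0), and state that they are not read as incremental value.
4. Delete *progressively richer*.
5. State that the single-source increments are estimates and do not rank the sources.

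Cost: two more model sets for each of T20 and TPost, and some rewording. No new data are needed. The drawback is more contrasts to report, with intervals that will be wide, especially on the 20% hold-out.

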**Methods and analysis:**

PREACT-digital is a subproject of the Research Unit FOR 5187 (PREACT), a large multicentre observational study in four outpatient clinics. PREACT channels state-of-the-art machine learning techniques identify predictors of non-response to CBT in ID. The study is currently running and will end in June 2026. Patients seeking CBT at one of four participating outpatient clinics are invited to join PREACT-digital. They can take part in (1) a short version with a 14-day EMA and passive sensing phase prior to therapy, or (2) a long version in which the short version’s assessments are extended throughout the therapy. It is estimated that 468 patients take part in PREACT-digital, of which 350 opt for the long version of the study. Participants are provided with a smartwatch and a customised study app. We collect passive data on heart rate, physical activity, sleep and location patterns. EMA assessments cover affect, ER strategies, context and therapeutic agency. Primary outcomes on (non)-response are assessed after 20 therapy sessions and therapy end. We employ predictive and exploratory analyses. Predictive analyses focus on classification of non-response using basic algorithms (ie, logistic regression and gradient boosting) for straightforward interpretability and advanced methods (LSTM, DSEM) to capture complex temporal and hierarchical patterns. Exploratory analyses investigate mechanistic links, examine the interplay of variables over time and analyse change trajectories. Study findings will inform more personalised and ecologically valid approaches to CBT for ID.

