### Outcomes

We use different machine learning techniques to predict treatment response based on DP data. To evaluate treatment response, we implement two different criteria. First, we follow the definition of the PREACT research group to achieve comparability with other subprojects. It follows the concept of clinically significant change as introduced by Jacobson & Truax.^29^ The shift from a dysfunctional to a functional mental condition is operationalised by achieving a Brief Symptom Inventory-General Severity Index (BSI–GSI) score of less than 0.56 at T20/posttreatment assessment. Additionally, the change observed from baseline to T20/posttreatment must be reliable, as defined by the Reliable Change Index (RCI). The BSI–GSI is a self-report measure assessed cross-sectionally at T20 and TPost as part of PREACT.

Second, we will use aggregates of EMA assessments on positive and negative affect (PANAS-X; 21) collected during measurement bursts at T20 and TPost as additional indicators of treatment response as EMA-based measures were shown to capture different aspects of symptom load (28).

To account for the complexity of ID, PREACT further included disorder-specific measures as secondary outcomes: The Hamilton Anxiety Rating Scale (HAM-A; 29), the Montgomery–Åsberg Depression Rating Scale (MADRS; 30), the Yale-Brown Obsessive Compulsive Scale (Y-BOCS; 31, 32) and the Clinician-Administered PTSD Scale for DSM-5 (CAPS-5; 33, 34).

Finally, for exploratory analyses, outcomes will depend on the respective research question, that is, single-beep scores of EMA constructs or cross-sectional self-reports of ER capacities.

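### Eight unadjusted paired AUC comparisons carry the incremental-value question; none is named as the main contrast, and the hypothesised gain of passive sensing over EMA is not among them

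*Protocol article*

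**What the plan says.** All references are to the protocol article.

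- **Predictive analyses** gives its interest as the value that digital data add to cross-sectional self-report. It first builds a model on intake information alone. Then: "The baseline cross-sectional models will be compared against four progressively richer model sets". The four sets are (a) EMA only, (b) passive sensing only, (c) EMA plus passive sensing, and (d) intake, EMA and passive data together.
- On outcome times, the same section says: "Separate models will be trained for our two prespecified outcomes (T20, TPost". The Abstract treats both as primary: "Primary outcomes on (non)-response are assessed after 20 therapy sessions and therapy end".
- On the test and level: "Paired differences in area under the curve (with 95% CIs, DeLong test) will quantify improvements in discrimination of (non)-response". No contrast or time is ranked, and no adjustment is mentioned.
- **Introduction** sets a first objective of predicting non-response at both times "with sufficient predictive accuracy (i.e. >75%) using a combination of EMA and passive sensing features collected during the first, 14-day assessment phase (T0". It also hypothesises that, beside EMA features, "passive features will provide significant incremental value".
- **Model development** places tuning and model selection in the development data and evaluates the optimised pipeline on the untouched 20% hold-out.

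**The concern.** The article separates predictive analyses, which carry stated hypotheses, from exploratory ones. Within the predictive part it fixes the contrasts, the test and the confidence level, but not which contrast answers the incremental-value question. Results could easily conflict: (d) might improve on baseline at T20 but not at TPost, or EMA alone might improve while passive sensing alone does not. With eight comparisons of equal standing, the headline could rest on whichever interval happens to exclude zero, and its error rate would no longer be that of a single test.

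The listed contrasts also do not match the stated questions. Most of them do not measure an increment over intake data, and the one that would test the passive-sensing hypothesis is absent.

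**Working it through.** **1. The plan's own figures.** From Sample size calculation: 585 × 0.80 = 468, as stated; 468 × 0.75 = 351, stated as 350. Both reproduce. The 585 cannot be re-derived, because its inputs lie in the main protocol. The article gives no error rate or power for the AUC comparisons. A 20% hold-out would be 0.20 × 468 = 93.6 (about 94) or 0.20 × 350 = 70 patients.

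**2. Number of comparisons.** 4 model sets × 2 times = 8.

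**3. Error rate if all are read as tests, no true differences, independent tests.** Any false difference: 1 − 0.95^m. At least one false improvement (richer model favoured): 1 − 0.975^m.

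| Comparisons m | Any false difference | At least one false improvement |
|---|---|---|
| 1 | 5.0% | 2.5% |
| 2 | 9.75% | 4.9% |
| 8 | 33.7% | 18.3% |

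**4. Allowing for correlation.** The eight tests share patients and a baseline model, so they are positively correlated. The paired DeLong tests were simulated with 3,000 runs per setting. All inputs are assumptions, since the article gives none:

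- 70 or 94 patients and non-response of 40% or 60%;
- a true AUC of 0.65 for every model;
- score correlations of 0.2-0.7 between models and 0.3-0.95 between times.

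Results across settings:

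- one test, any difference: 4.9-5.8%;
- eight tests, any false difference: 23.0-30.0%;
- eight tests, at least one false improvement: 11.6-15.7%;
- eight tests at 0.05/8 = 0.00625 each: 3.8-5.9% for any difference and 1.8-3.6% for an improvement.

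**5. What each contrast measures.**

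| Contrast | Intake predictors in both models? | Question answered |
|---|---|---|
| (a), (b) or (c) vs baseline | No | Can digital data replace intake data? |
| (d) vs baseline | Yes | Do digital data add to intake data? |
| (c) vs (a) | Neither has them | Does passive sensing add to EMA? (not listed) |

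Only (d) versus baseline matches the section's stated interest in increment. Only (c) versus (a) isolates what passive sensing adds to EMA.

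**6. The accuracy target.** The >75% criterion applies to EMA plus passive features, which is set (c). It concerns accuracy rather than AUC, has no comparator model and covers both times. It can answer whether prediction is good enough, but not whether digital data improve on intake data.

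**The case against.** The strongest reply is that this is a condensed article on an observational prediction study. Multiplicity rules normally sit in an analysis plan, and the article points to OSF and GitHub for the analysis procedure. This stands as far as it goes: the missing adjustment alone would not be a finding. It does not cover the choice of contrasts, which the article itself sets out together with the test and level, and which do not line up with its own hypotheses.

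A second reply is that the AUC sentence speaks of quantifying and gives no rule by which one interval excluding zero counts as success. That is correct, so the error rates are conditional on a testing reading. The named significance test and the Introduction's reference to significant value make that reading natural, but the text does not compel it.

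A third reply is that (a)-(c) and (d) ask different questions, so an at-least-one-of-eight rate matters only if any single success would support one joint claim. That is fair, and it is a further reason to state which contrast supports which claim.

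Four stronger readings are tempting but not supported:

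- **That a false claim is likely.** Under independence, passing 50% takes 14 comparisons for any difference (ln 0.5 / ln 0.95 = 13.5) or 28 for a false improvement (ln 0.5 / ln 0.975 = 27.4). Eight do not reach it.
- **That there are really 16 tests or more.** Outcomes says "To evaluate treatment response, we implement two different criteria", but the second criterion is an EMA affect aggregate with no response cut-off given, so an AUC does not follow. The choice among algorithms would multiply tests only if several were tested on the hold-out, and Model development puts selection in the development data.
- **That nothing decides the prediction question.** The >75% target addresses it, although not the incremental question.
- **That all eight tests are certainly run on the hold-out.** This is a reasonable inference, but the article does not say which data the DeLong comparisons use.

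**Conclusion.** The point holds in a limited form. The plan fixes eight paired AUC comparisons at two unranked primary times, each with an unadjusted 95% interval and DeLong test, and names no main one. It gives (d) versus baseline, the only contrast that measures the gain over intake data, the same standing as three replacement contrasts, and it omits the contrast for its own passive-sensing hypothesis.

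If all eight are read as tests, the chance of at least one false improvement is 18% under independence and about 12-16% under the assumed correlations. That is roughly five to seven times the 2.5% for one test. These figures assume that every model truly has equal AUC. If EMA-only or passive-only models truly discriminate less well than the baseline, the chance of a false improvement is lower. The mismatch between hypotheses and listed contrasts rests on no such assumption. The change is worth making, because a main contrast carries weight only if it is fixed before the hold-out results are seen.

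**What to change.** Before the hold-out is opened, add to Predictive analyses and the OSF record:

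1. The main contrast is (d) versus the intake-only baseline for BSI-GSI non-response, with one pipeline per model set locked on the development data and the paired AUC difference tested on the hold-out at two-sided 5%.
2. It is tested at one pre-named time, and at the other only if the first succeeds. Whether T20 or TPost comes first is the group's choice, provided it is fixed beforehand. The fixed sequence keeps the main claim at 5% (2.5% for improvement).
3. The contrast for the passive-sensing hypothesis is (c) versus (a). Say whether it follows in the same sequence or stands as a separate question at its own level. At one time each, two such contrasts give up to 1 − 0.975² = 4.9% for at least one false improvement under independence.
4. All other contrasts are reported with 95% CIs and labelled exploratory, or Holm-adjusted if claims are wanted.
5. The >75% accuracy target is a separate criterion from the AUC comparisons.

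The cost is a few sentences and no new data. The small downside is that fewer contrasts can be presented as confirmatory.
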